### Subgroup Analyses

We will analyze subgroups based on weekdays of randomization: Mondays and Tuesdays versus Wednesdays, Thursdays, and Fridays. We hypothesize that the treatment effect will be less among patients randomized mid to late week as they may have longer stay because their postsurgical recovery is more likely to overlap with weekends where there may be operational delays in discharge, such as the absence of physiotherapists, that cannot be influenced by knowledge of VC-RAM allocation. To examine this, we will include interaction terms between group assignment and weekday randomization into the Cox regression model, with significant interaction inferred at a *P* value of <.05.

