### Randomization

Randomization occurs before surgery, after eligibility is confirmed, and informed consent is obtained. We randomize as close to the time of surgery as possible to minimize the risk of surgery postponement. Patients are randomized using an Interactive Web Randomization System, a 24-hour computerized system maintained by the coordinating center at the Population Health Research Institute, a joint institute of Hamilton Health Sciences and McMaster University in Hamilton, Ontario, Canada.

The randomization process uses block randomization with varying block sizes stratified by site, ensuring that study personnel and investigators remain unaware of block sizes. Patients are randomized in a 1:1 ratio to receive VC-RAM or standard care. Following randomization, research personnel notify the patient’s surgeon and the patient of the treatment allocation. Patients, health care providers, and data collectors are aware of treatment assignments, while outcome adjudicators remain blinded to treatment allocation.

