### Statistical Analyses

We will analyze all data according to a prespecified statistical analysis plan developed and finalized before any investigator is unblinded.

Following the intention-to-treat principle, we will analyze patients in the treatment groups to which they were randomized. For both coprimary outcomes, we will compare all patients allocated to the PVC-RAM-3 intervention to all patients allocated to standard care.

For coprimary 1 (composite of hospital readmission or emergency department visit), we will compute the time to event from the discharge date and plot the cumulative incidence curves between the two treatment groups. We will use a Cox regression model to obtain hazard ratios and 95% CIs. Any acute hospital care event that occurs before patients undergo their index surgery, in cases where surgery is postponed, will not be included in this outcome.

For coprimary 2 (index hospital LOS), we will calculate the hospital LOS for both groups and compare them with a 2-sample Wilcoxon rank sum test. Given the large sample size, the 2-sample Wilcoxon rank sum test will produce results that will be similar to the 2-sample *t* test.

For the coprimary outcome analyses, we will censor patients whose surgeries were canceled and not rescheduled within 30 days of randomization.

VC-RAM will be considered effective if either of the 2 coprimary efficacy analyses is significant. We will use a gatekeeping with a fallback procedure to analyze their statistical significance [12]. We will start with an overall α of .05, split between the two outcomes with a computed 2-sided *P* value less than an α of .04 for postdischarge acute hospital care and less than an α of .01 for index length of hospital stay. If the first coprimary outcome achieves significance at an α level of <.04, the α from this test will be added to the second coprimary outcome’s α (ie, the α will be .05). However, if the first coprimary outcome is not significant, the second coprimary outcome will be tested at an α level of <.01.

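### The weekday subgroup analysis states a length-of-stay hypothesis but, read literally, tests it in the Cox model for post-discharge acute hospital care

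*Protocol article*

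**What the plan says.** Under Subgroup Analyses the article gives a single factor: "We will analyze subgroups based on weekdays of randomization: Mondays and Tuesdays versus Wednesdays, Thursdays, and Fridays". It predicts that "the treatment effect will be less among patients randomized mid to late week as they may have longer stay", and attributes this to weekends that bring "operational delays in discharge, such as the absence of physiotherapists, that cannot be influenced by knowledge of VC-RAM allocation". For the test, "we will include interaction terms between group assignment and weekday randomization into the Cox regression model", with significance at P<.05. The section does not name an outcome.

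Under Statistical Analyses one Cox model is described. It belongs to the first coprimary outcome, readmission or an emergency visit after discharge, for which "we will compute the time to event from the discharge date and plot the cumulative incidence curves between the two treatment groups". For the second coprimary outcome, index length of stay, the plan is to calculate the stay in each group and "compare them with a 2-sample Wilcoxon rank sum test". The other regression models in that section (log-binomial, analysis of covariance) are for secondary and tertiary outcomes. No regression or time-to-discharge model for index stay appears.

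On timing, Trial Outcomes starts the length-of-stay clock at the end of surgery. Randomization places allocation before surgery: "We randomize as close to the time of surgery as possible to minimize the risk of surgery postponement". Statistical Analyses foresees operations postponed after randomisation.

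**The concern.** The reasoning behind the subgroup is about when patients leave hospital. The Objective in the abstract says that telling surgeons and patients the allocation is what should bring discharge forward, so a barrier that such knowledge cannot shift is a barrier to the length-of-stay effect. The model named for the test starts its clock once the index stay is over and measures something else.

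If the text is followed, the interaction P value concerns whether the acute-care hazard ratio differs by weekday. A null result would not count against the weekend hypothesis, and a significant one would not support it. The Discussion itself says that the relation between length of stay and readmission is unclear, so the acute-care result cannot stand in for the stay result.

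A lesser concern is the grouping variable. Whether recovery meets a weekend depends on the day of surgery, while patients are grouped by the day of randomisation.

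**Working it through.** **1. Hypothesis against model.**

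| | Hypothesis (Subgroup Analyses) | The Cox model (Statistical Analyses) |
|---|---|---|
| Outcome | Delay in index discharge | Readmission or emergency visit |
| Clock | From end of surgery to discharge | From discharge onwards |
| Active component | Knowledge of allocation | Monitoring after discharge |

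The Wilcoxon test planned for stay compares two groups and has no interaction term. No described analysis therefore joins the hypothesis to its own outcome. This step needs no assumption.

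**2. Design figures used in the illustration.** The subgroup section states no power, so the inputs come from Sample Size Calculations.

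- Acute care: 14% against 9.8%, 1250 per arm, two-sided alpha .04. Events = 1250 × 0.14 + 1250 × 0.098 = 297.5. HR = ln(0.902)/ln(0.86) = 0.684. Schoenfeld power = Φ(√297.5/2 × |ln 0.684| − 2.054) = 88.9%, against the stated 88.7%. The figure reproduces.
- Stay: a 1-day reduction in 35% of patients is a mean shift of 0.35 day. Table 2 gives N = 2356 for 80% power at alpha .01. By the t-test formula, SD = 0.35/√[2(2.576 + 0.842)²/1178] = 2.49 days. The article states no SD; this one is implied.

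**3. Size of the outcome mismatch.** Assumptions not in the article: surgery spread evenly over Monday-Friday, giving 1250 × 2/5 = 500 and 1250 × 3/5 = 750 per arm in the two strata; and the whole average stay effect in the early-week stratum, 0.35/0.4 = 0.875 day against 0.

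- Standard error of the interaction on stay = 2.49 × √(2/500 + 2/750) = 0.203 day.
- Power at P<.05 = Φ(0.875/0.203 − 1.96) = 99%. A 4000-run simulation with SD 2.5 gave 98.8%.
- In the same simulation, with an acute-care hazard ratio of 0.70 in both strata, the acute-care interaction (a comparison of log rate ratios standing in for the Cox term) rejected in 5.35% of runs. That is its alpha, as it must be when the hazard ratio does not vary.
- With a smaller contrast, 0.35 day against 0, power for the interaction on stay is Φ(0.35/0.203 − 1.96) = 41%.

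**4. The weekday proxy.** With an expected stay of up to 3 days (Trial Population), the cut suits the day of surgery: Tuesday + 3 is Friday, Wednesday + 3 is Saturday. The lag from randomisation to surgery is not given, so a range is shown, again with an even spread over Monday-Friday. Share of the surgery-day contrast kept = P(early surgery | grouped early) − P(early surgery | grouped late).

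| Lag | Surgery days grouped early | Surgery days grouped late | Share kept |
|---|---|---|---|
| Same day | Mon, Tue | Wed, Thu, Fri | 1 − 0 = 100% |
| 1 working day | Tue, Wed | Thu, Fri, Mon | 1/2 − 1/3 = 17% |
| 2 working days | Wed, Thu | Fri, Mon, Tue | 0 − 2/3 = −67% |

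A reader might count only Friday randomisations (Monday surgery) at the one-day lag and infer a loss of about a third. Tuesday randomisations (Wednesday surgery) move too, so the loss is 5/6.

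**The case against.** The strongest reply is that a Cox model for time to discharge was meant. Length of stay was the sole primary outcome until late in the trial (Trial Outcomes), and Statistical Analyses speaks of censoring patients with cancelled surgery in both coprimary analyses, which is time-to-event language. The analysis plan, which is not shown, may define such a model. This is plausible, and it rules out the stronger inference that the trial cannot answer its weekend question. It does not remove the mismatch: the article refers to the Cox model as one already described, and only the acute-care model fits. This is a stated hypothesis paired with a stated test that does not match it, rather than a detail left to another document.

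On the weekday, a reader might infer that the subgroups are misclassified. The article does not show that. Its aim of randomising close to surgery points to a short lag, and with same-day randomisation nothing is lost. Weekday of randomisation is also a clean baseline factor, and the scheduled surgery weekday would equally stay fixed if an operation were postponed.

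Finally, this is one subgroup test, and 41% power for a modest contrast means that a null interaction on stay would be weak evidence even in the right model. Both points stand, and they limit the importance of the issue.

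**Conclusion.** The outcome mismatch holds on the article's own text without any assumption: as written, a hypothesis about discharge delay is tested on post-discharge acute care. The 99% against 5% contrast illustrates this, and rests on an implied SD of about 2.5 days, an even weekday spread, the whole stay effect in one stratum and a constant acute-care hazard ratio. The size of the true contrast is unknown.

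The weekday point is secondary and conditional. The effect ranges from none with same-day randomisation to a reversed contrast at two working days, and the article does not say where in that range the trial lies.

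The coprimary tests, the alpha split and the stated power are untouched. The point should be corrected but does not threaten the main result.

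**What to change.** - Name index length of stay as the outcome of the weekday subgroup analysis.
- Test the group-by-weekday interaction in a model for stay: proportional odds, which is close in spirit to the Wilcoxon test; linear with robust standard errors; or a time-to-discharge model that is explicitly defined. Report the difference in stay within each subgroup with confidence intervals.
- Keep any weekday interaction in the acute-care Cox model as a separate exploratory analysis with its own rationale.
- Report the distribution of the lag between randomisation and surgery. If the surgery date scheduled at randomisation was recorded, group by its weekday, at least as a sensitivity analysis.
- Recruitment and follow-up are complete and analysis is underway, so document the change before investigators are unblinded, or label it post hoc.

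The cost is a few lines of text and one additional model. Actual surgery times must be held, because stay is computed from them. The article does not say whether scheduled dates were kept; if they were not, the regrouping by scheduled weekday is unavailable and the rest of the fix still applies.

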### Interim Analyses

Two interim efficacy analyses based on the primary outcome occurred when 50% and 75% of the patients had been followed for 30 days. The data monitoring committee (DMC) used the modified Haybittle-Peto rule of 4 SDs (α=.0000633) for analyses in the first half of the trial (including the first planned interim analysis) and 3.5 SDs (α=.0004653) for all analyses in the second half. For a finding of the treatment to be considered significant, these predefined boundaries had to have been exceeded in at least two consecutive analyses, 2 or more weeks apart. The interim analyses were conducted under protocol version 1.0 dated December 22, 2021, and therefore, did not take into consideration the changes made to the primary outcome in protocol version 2.0 dated January 25, 2025.

### Ethical Considerations

This trial is conducted in compliance with the protocol, the principles outlined in the Declaration of Helsinki, and Good Clinical Practice. The Hamilton Integrated Research Ethics Board provided its approval for the protocol and consent form (project ID 14365) before initiating the study. Research personnel obtain informed consent for each patient before randomization. All patient information is stored in a high-security computer system and kept strictly confidential. Participant confidentiality is further ensured by using identification code numbers to correspond with treatment data in computerized files. Medical information obtained during the trial is considered confidential and is not disclosed to third parties. However, this information may be shared with the patient’s personal physician or other appropriate medical personnel responsible for the patient’s care.

### Trial Organization

The Population Health Research Institute is the sponsor and coordinating center for this trial, overseeing trial organization, randomization scheme development, study database creation, data consistency checks, data analysis, and study center coordination. The trial structure includes a project office, operations committee, steering committee, DMC, site principal investigators, coinvestigators, and adjudication committee. The coprincipal investigators, project officers, program manager, and research coordinator are responsible for the activities of the Project Office. If safety concerns arise during the trial, the DMC Chair convenes a formal committee meeting. The DMC reviews all available data and relevant external studies before making recommendations to the Project Office Operations Committee. If termination is considered, the committee explores all alternatives before a decision is made. A detailed charter governs the DMC’s activities. Details about trial groups and investigators are provided in Multimedia Appendix 8.

## Results

The first patient was randomized on December 29, 2021, and recruitment of the target 2500 patients was completed on October 25, 2024. The DMC conducted the first and second scheduled interim analyses and recommended continuing the trial. The final version of the study protocol was submitted prior to the unblinding of the trial investigators. Some protocol amendments were implemented during the trial, with the most recent version finalized near the end of the study period. This paper is based on the most recent version of the study protocol (version 2.0, January 1, 2025). The data will be analyzed, and the study results will be published in a separate paper.

## Discussion

### Overview

Reducing postdischarge acute hospital care and index length of hospital stay remains a critical unmet need for surgical patients. We hypothesize that VC-RAM holds significant potential to address these challenges by lowering the incidence of these key outcomes. Building on the lessons learned from the PVC-RAM-1 trial, which established a scalable and effective model for VC-RAM, the PVC-RAM-3 trial adapts the intervention for elective surgical populations and examines how presurgical knowledge of VC-RAM allocation influences discharge decisions.

Throughout the last decade, there have been substantial changes in the duration of hospital admission for some surgical interventions. The relationship between the length of hospital stays and readmission rates is unclear, as some research indicates that shorter hospital stays are associated with higher readmission rates, while other studies suggest that longer stays may lead to more readmissions [2,13]. To the extent that shorter hospital stays may result in the need for more acute hospital care post discharge, this identifies a greater need for interventions to decrease acute hospital care post discharge, an objective that our VC-RAM intervention seeks to address. Our inclusion of patients undergoing elective surgery with an expected LOS of ≤3 days in this trial focus on a lower-risk population, where hospital discharge is less likely to be delayed by competing comorbidities. This targeted approach allows for a meaningful evaluation of VC-RAM’s ability to safely shorten hospital stays and optimize postdischarge care. Previous evidence has not identified significant safety risks associated with VC-RAM [8], supporting its feasibility for broader implementation.

With our VC-RAM intervention, when escalation triggers are met, nurses promptly escalate care to the perioperative physicians. These physicians can then take several actions depending on the patient’s needs, including continuing remote monitoring, conducting a video visit, referring the patient to an outpatient diagnostic facility, initiating or altering medications, or arranging follow-ups with themselves or nonstudy doctors, such as the surgeon or family physician. These measures are designed to manage complications within the community or through virtual care, thereby reducing the necessity for acute hospital visits.

PVC-RAM-3 trial is powered to detect a 30% relative risk reduction in acute hospital care and a 1-day reduction in index LOS in at least 35% of patients. With estimated baseline rates of 20%-25% for acute hospital care and an average hospital stay of 2.5 days [7], a 30% reduction could prevent 6-7.5 acute care visits per 100 patients. Postpandemic elective surgery volumes for those meeting PVC-RAM-3 inclusion criteria is approximately 4500 surgeries per year. If we reduce the LOS by a day for 30% of these elective surgeries, we could free up hospital beds and increase surgical volume by an additional 1350 cases per year to address surgical backlogs. This has the potential to generate substantial cost savings for the health care system.

Our previous trial demonstrated the potential of VC-RAM to improve other patient-important outcomes, such as the identification and correction of drug errors, pain management, and the medical optimization of patients, including those with atherosclerotic disease, for whom proven secondary prevention therapies exist, and those who smoke tobacco [8]. However, significant opportunities remain to further optimize pharmacological therapy to enhance long-term health outcomes, and these are evaluated in PVC-RAM-3.

### Strengths and Limitations

This is a large randomized controlled trial that evaluates the impact of knowledge of assignment to receive VC-RAM on index LOS and VC-RAM on postdischarge acute hospital care. The intervention builds on our prior VC-RAM studies and is optimized for efficiency by shortening the intervention period from 30 to 14 days, reducing wound photo duration to 7 days, and strictly enforcing vital signs' escalation thresholds across all centers. A potential limitation of this study is the burden of frequent monitoring and patient contacts, as well as the possibility that the resources required to deliver the intervention may offset in-hospital cost savings in settings outside our health system, thereby limiting generalizability. However, a separate economic evaluation is planned to address this issue.

### Dissemination

We will disseminate findings through presentations at national and international conferences, publications in high-impact peer-reviewed journals, and posts on the “Reducing Global Perioperative Risk” Resource Center, a global multimedia platform linked to Elsevier’s online readership.

### Conclusions

The results of the PVC-RAM-3 trial will provide critical insights into the role of VC-RAM in addressing current health system pressures and enhancing perioperative care globally.

## Appendix

Multimedia Appendix 1 SPIRIT (Standard Protocol Items: Recommendations for Interventional Trials) checklist.

Multimedia Appendix 2 Consent form.

Multimedia Appendix 3 Example of vital sign thresholds and recommend nurse and physician actions.

Multimedia Appendix 4 Additional details on nurse and physician actions.

Multimedia Appendix 5 Outcome Definitions.

Multimedia Appendix 6 Sample size.

Multimedia Appendix 7 Economic Analysis.

Multimedia Appendix 8 Trial Groups and Investigators.

## Abbreviations

DMC: data monitoring committee
LOS: length of stay
PVC-RAM-1: Post Discharge After Surgery Virtual Care with Remote Automated Monitoring Technology-1
PVC-RAM-3: Post Discharge After Surgery Virtual Care with Remote Automated Monitoring Technology-3
RAM: remote automated monitoring
SPIRIT: Standard Protocol Items: Recommendations for Interventional Trials
VC-RAM: virtual care with remote automated monitoring
